**Fig 1 pone.0248950.g001:**
[figure not shown]
Recommended content for the schedule of enrolment, interventions, and assessments. *Recommended content can be displayed using various schematic formats. See SPIRIT 2013 Explanation and Elaboration for examples from protocols. **List specific timepoints in this row. *t*_*1*_: postpartum day 1, *t*_*2*_: postpartum day 2, *t*_*3*_: postpartum day 3, *t*_*4*_: six months postpartum.

The volume of the breastmilk will be evaluated. The sum of the weight difference in gram will be converted into the volume of the breastmilk in milliliter (1 g = 1mL). This method is comparable with the measurement of the volume of the breastmilk based on deuterium oxide dilution technique from a previous study [9–11].

Time to noticeable breast fullness is defined as the mean time from birth to noticeable breast fullness. The participants will be asked if they noticed their breasts were full and followed by ‘When did you feel breast fullness?’.

Satisfaction and quality of life will be asked at postpartum day 7 via a phone interview. Satisfaction answer choices will consist of the following: very satisfied, satisfied, neutral, unsatisfied, and very unsatisfied. Quality of life will be assessed by WHOQoL-BREF [12]. The participants will be asked with “Did the capsules help?”. Side effects are recorded at postpartum day 3 by interview and at postpartum day 7 via a phone interview. The exclusive breastfeeding rates and any breastfeeding at 6 months will be asked via a phone interview.

The sample size calculation is based upon the findings from a previous study [13]. Two-tailed test is used. The average volume of breastmilk on 3 days postpartum was 135.0 ± 61.5 mL. We expect that there will be a 30% increase in the volume of the breastmilk. With adjustments for a withdrawal rate of 20%, a minimum of 44 women in each group are required to detect statistical difference (α = 0.05, β = 0.2) between the two groups. Therefore, a total of 88 women are required for this study.

Data monitoring committee (DMC) is not needed in this study due to a short duration of the trial and known minimal risks. Interim analyses will not be performed in this trial due short duration of recruitment and no potentially serious outcomes. No adverse effects were reported in human studies. However, the risk and harm are monitored. Both type of risk and severity are monitored. Side effects (such as constipation, nausea/vomiting, diarrhea, heartburn, hypotension, hypoglycemia) and serious adverse effects/serious adverse reactions both in mother and especially vulnerable newborn (such as neonatal hypoglycemia, hypotension) are monitored. Harm will be monitored and report to Research Ethics Committee of the Faculty of Medicine, Chulalongkorn University. Auditing will be performed by research nurses who are not involved in the study every 3 months. Investigators plan to provide care for participants’ healthcare needs that arise as a direct consequence of trial participation and pay for compensation to those who suffer harm from trial participation.

Principal investigators will have access to the final trial dataset. Investigators plan to communicate trial results to participants and send for publication in peer reviewed journal.

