The nurses will enroll the participants. As soon as the participant meets the inclusion criteria, the nurses will proceed to select a sequentially numbered opaque envelope. The opaque envelopes will contain 6 capsules of Moringa oleifera leaves powder or placebo (identical in size, shape, and color). The opaque envelopes are sealed to ensure the allocation sequence is secure. The treatment group will receive Moringa oleifera leaves powder (450mg per capsule) (Ouay Un Osoth, Thailand) and the placebo group will receive no drug capsules. All women will take 1 capsule of the Moringa oleifera or placebo 2 times before meal for 3 days. Participants will take their first capsule at first 6 hours of birth. Treatment assignment will not be revealed until data collection is completed 6 months later. All women will be admitted into the postpartum ward and discharged on the fourth day postpartum. Hence, all women will receive all of their medications. The research nurses will capture the measures outcome and 8 personnel involve in this study. The dosage of 450 mg Moringa oleifera leaves powder is used in the study due to the recommendation from Thai traditional medicine for galactagogue. This dosage is higher than previous studies [6, 7].

The primary outcome is the volume of breastmilk on the third day postpartum. Secondary outcomes will assess the delta daily milk volume of consecutive 3 daily postpartum, time to noticeable breast fullness, the maternal satisfaction, quality of life, side effects, and the exclusive breastfeeding rates at 6 months (Fig 1). The third day is used as the measurement time point because it represents the timing of stage II lactogenesis [6]. The weighing method will be used on the third day postpartum (48–72 hour). The weighing procedure will start at 48 hours after delivery in all women. The nurse will weigh the infant fully clothed before and after each feeding using an electronic weight scale (Camry ER 7210, accurate to 5 g) for the period of 24 hours. The numbers of times weight measures taken will be 8–12 depending on frequency of breastfeeding of each participant. The baby would be weighed each time she/he wants to feed, even if it’s a baby who wants the breasts every 20 minutes.

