### Statistical analysis

IBM SPSS version 22 (SPSS: An IBM Company, New York, USA) will be used for statistical analysis. Two-tailed test is used in this study. Kolmogorov-Smirnov tests will be used to assess data distribution prior to statistical analysis. Chi-square test and Fisher’s exact test will be used for categorical variables such as percentage of satisfaction and side effects. Independent t-test will be used for parametric continuous variables such as the volume of the breastmilk. Mann-Whitney U test will be used for nonparametric variables when appropriate. A p-value <0.05 will be considered statistically significant. Analysis of the trial will be conducted by using intent-to-treat (ITT) analysis (Fig 2).

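### Hypotension and hypoglycemia are listed as side effects, but the only recording method stated for side effects is interviewing the mother, which can miss symptom-free events

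*Protocol article*

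**What the plan says.** All the relevant text is in the protocol article, under Materials and methods and its Statistical analysis subsection.

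- The secondary outcomes include "quality of life, side effects, and the exclusive breastfeeding rates at 6 months".
- The recording method for this outcome is given in one sentence: "Side effects are recorded at postpartum day 3 by interview and at postpartum day 7 via a phone interview".
- The harm-monitoring paragraph, after the sample size, says what the term covers: "Side effects (such as constipation, nausea/vomiting, diarrhea, heartburn, hypotension, hypoglycemia". The list closes there, with six examples.
- The same sentence adds serious adverse effects and reactions, "both in mother and especially vulnerable newborn (such as neonatal hypoglycemia, hypotension) are monitored". Just before it stands the general statement "Both type of risk and severity are monitored". Neither comes with a method, threshold or schedule.
- On the setting: "All women will be admitted into the postpartum ward and discharged on the fourth day postpartum". The capsules are taken over three days, so the dosing period is spent on the ward.
- On the analysis: "Chi-square test and Fisher’s exact test will be used for categorical variables such as percentage of satisfaction and side effects".

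**The concern.** Four of the six listed side effects (constipation, nausea or vomiting, diarrhea, heartburn) are symptoms, and asking the woman is a sensible way to record them. Hypotension and hypoglycemia are different. They are defined by a blood pressure or glucose value, and a mild episode may produce nothing she would notice or name. The article does state a recording method, and that method does not suit two of the effects it is meant to cover. This is a poorly matched choice, not just a detail left out.

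At stake is what the trial can say about safety. If symptom-free episodes go unrecorded, the counts that enter the chi-square or Fisher's exact test are too low. A table with no hypotension or hypoglycemia could then be taken as evidence of absence when nobody had looked with an instrument. The primary outcome, milk volume on day 3, is not touched.

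**Working it through.** **Matching effect to method**

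| Listed event | Listed as | Recording route stated | Does the route fit? |
|---|---|---|---|
| Constipation, nausea/vomiting, diarrhea, heartburn | Side effect | Interview on day 3, phone on day 7 | Yes, self-reported symptoms |
| Hypotension, hypoglycemia (mother) | Side effect | The same interviews | Only for episodes with symptoms, or a diagnosis she was told of |
| Hypoglycemia, hypotension (newborn) | Serious adverse effect | None stated | Cannot be judged |

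**The plan's own figure.** The denominator is 44 per group. The sample-size paragraph gives a mean of 135.0 mL, SD 61.5 mL, a 30% increase (40.5 mL), two-sided α = 0.05 and power 0.80. The normal approximation gives 36.2 per group, and 36.2 × 1.2 = 43.4, rounded up to 44. The stated 44 reproduces. It was chosen for milk volume and is used here only as the number at risk.

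**What zero events would show with full detection.** The exact one-sided 95% upper limit solves (1 − p)^44 = 0.05:

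p = 1 − 0.05^(1/44) = 0.066, or 6.6%.

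If the planned 20% withdraw, 44 × 0.8 ≈ 35 remain, and 1 − 0.05^(1/35) = 8.2%.

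**What incomplete detection does.** Let p be the true risk and s the share of events that an interview picks up. The chance of recording no event in one arm is (1 − p·s)^44. The documents give neither p nor s, so every value below is an assumption, shown for direction and range only.

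| Assumed p | s = 1 | s = 0.5 | s = 0.25 | s = 0.1 |
|---|---|---|---|---|
| 2% | 0.41 | 0.64 | 0.80 | 0.92 |
| 5% | 0.10 | 0.33 | 0.57 | 0.80 |
| 10% | 0.01 | 0.10 | 0.33 | 0.64 |

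The upper limit after zero recorded events becomes 6.6%/s, for example about 13% at s = 0.5 and 26% at s = 0.25. These figures only restate the assumed s. They are not estimates for this trial.

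The first column matters too. At an assumed risk of 2%, an arm of 44 shows no event with probability 0.41 even when nothing is missed.

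**The case against.** The strongest reply is that the article does not confine safety data to interviews. It says separately that type and severity of risk are monitored and that harm is reported to the ethics committee. The women are inpatients throughout dosing, and a condensed article may leave the monitoring method to the full protocol. This stands in part: interview is the only *stated* method for the side-effect outcome, not demonstrably the only source of safety data. It does not remove the mismatch, because the article assigns a recording method to side effects and counts hypotension and hypoglycemia among them.

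Several stronger readings are tempting and are not supported:

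- *Newborn harms are recorded by asking the mother.* The article puts newborn hypoglycemia and hypotension under serious adverse effects, while the interview sentence concerns side effects. No route is stated for the newborn events.
- *Interview cannot detect these events.* A mother can report a symptomatic episode or a diagnosis made on the ward. What interview can miss is the silent event.
- *Unmeasured events will be counted as absent, or the trial will show none.* The article gives no coding rule for unassessed participants. Whether none is recorded depends on a risk and a detection share that it does not give, and rare events may be absent from 44 women even with full detection.
- *The safety reassurance is borrowed from lower-dose studies.* The article does say of its own regimen "This dosage is higher than previous studies", but that remark cites references 6 and 7, whereas the statement that human studies reported no adverse effects cites reference 4. The documents do not link the two.

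A fair objection also applies to the remedy. No passage says that blood pressure or glucose values exist in the charts. If tests were prompted by symptoms, a rate among those tested would come from a group selected after randomization and enriched for events. The fix has to guard against this.

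**Conclusion.** The point holds in limited form. For maternal hypotension and hypoglycemia, the only recording method stated for the outcome is self-report, which can miss episodes without symptoms and so biases the recorded counts toward none. This assumes that some episodes are silent and that false reports do not make up for them. The size of the bias cannot be derived from the documents. The one firm figure is that zero events in 44 would exclude a risk above 6.6% (one-sided 95%), and that needs full detection; with less, the limit is weaker by an unknown factor.

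For the newborn, the finding is only that events said to be monitored have no stated recording route or definition. The primary outcome and the sample size are unaffected. The change is worth making because the outcome is named and tested and the remedy is cheap.

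**What to change.** - Keep the day 3 and day 7 interviews for symptoms.
- For hypotension and hypoglycemia in mother and newborn, also abstract any blood pressure and glucose values and any diagnoses already in the ward charts, from the first capsule to discharge on day 4.
- Apply one written definition of each event, fixed before unblinding. The article keeps the assignment concealed until data collection ends at 6 months, which leaves time for this.
- Report event counts by arm over all randomized pairs and, beside them, the number in each arm with any measurement.
- Code a mother or infant without a value or diagnosis as not assessed, and do not read that as no event. Do not calculate rates only among those tested.
- State the recording route for the newborn events.

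The cost is chart abstraction for 88 mother-infant pairs and a few form fields. The charts may hold few newborn or glucose values, in which case the safety statement becomes narrower, though the reader will see why. No new measurement and no change of care is proposed.

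### Under the protocol's own inputs, allowing for 20% withdrawal takes about 46 to 48 women per group, not the stated minimum of 44 (minor)

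*Protocol article*

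**What the plan says.** The sample-size paragraph in Materials and methods of the protocol article takes its planning values from one previous study: "The average volume of breastmilk on 3 days postpartum was 135.0 ± 61.5 mL". The anticipated effect is relative: "We expect that there will be a 30% increase in the volume of the breastmilk". The test is two-sided ("Two-tailed test is used"), and the error rates are given where the number is said to be "required to detect statistical difference (α = 0.05, β = 0.2) between the two groups". The result is "With adjustments for a withdrawal rate of 20%, a minimum of 44 women in each group are required to detect statistical difference", followed by "Therefore, a total of 88 women are required for this study".

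The paragraph prints neither the number per group before the withdrawal allowance nor the way the allowance was applied. The Statistical analysis section names the test for the primary variable: "Independent t-test will be used for parametric continuous variables such as the volume of the breastmilk".

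**The concern.** The sentence makes a checkable claim: 44 per group is the smallest number that keeps 80% power when 20% withdraw. To retain a required number of evaluable women after a proportion w is lost, that number must be divided by (1 − w). For w = 0.20 this is division by 0.8, a factor of 1.25. Multiplying by 1.2 is a common slip and gives too few. The stated 44 is lower than the number that division gives from the article's inputs.

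At stake is the accuracy of the only justification given for the size of the trial. A reader who applies the standard adjustment to the printed inputs will not arrive at 44, and the power at the stated withdrawal rate is a little lower than claimed.

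**Working it through.** **Inputs, all from the sample-size paragraph unless noted**
- Control mean 135.0 mL. SD 61.5 mL, reading the ± figure as an SD and assuming the same SD in both groups.
- Difference: 0.30 × 135.0 = 40.5 mL. Standardised: 40.5 / 61.5 = 0.659.
- Two-sided alpha 0.05 and power 0.80, so z = 1.960 and 0.8416.
- Withdrawal 20%, equal groups.
- Independent t-test (Statistical analysis section).

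**Step 1. Evaluable women per group**

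Normal approximation: n = 2 × (1.960 + 0.8416)² × (61.5 / 40.5)² = 36.20, rounded up to 37.

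t-test (noncentral t): n = 37.18, rounded up to 38. As a check, t-test power is 79.8% with 37 per group and 80.9% with 38.

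**Step 2. Reproducing the stated 44**

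36.20 × 1.2 = 43.44, rounded up to 44. This matches with no input altered. It does require carrying the unrounded 36.20, because 37 × 1.2 = 44.4 would round up to 45.

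**Step 3. Allowance by division**

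| Base per group | Divided by 0.8 | Randomised per group | Total |
|---|---|---|---|
| 36.20 (normal, unrounded) | 45.25 | 46 | 92 |
| 37 (normal, rounded up) | 46.25 | 47 | 94 |
| 37.18 (t-test, unrounded) | 46.48 | 47 | 94 |
| 38 (t-test, rounded up) | 47.5 | 48 | 96 |

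Every route exceeds 44. The gap is 2 to 4 per group, or 4 to 8 in total.

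**Step 4. What 44 per group delivers**

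44 × 0.8 = 35.2, so about 35 per group remain after 20% withdrawal.

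| Evaluable per group | Power, normal | Power, t-test |
|---|---|---|
| 35 (20% lost) | 78.7% | 77.5% |
| 37 | 80.9% | 79.8% |
| 38 | 81.9% | 80.9% |
| 44 (none lost) | 87.1% | 86.3% |

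With 35 per group, the difference detectable with 80% power is 41.2 mL (normal, 30.5% of 135.0) or 41.8 mL (t-test, 30.9%), against the planned 40.5 mL (30%).

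**Step 5. Withdrawal that 44 can absorb at 80% power**

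In whole women: 1 − 38/44 = 13.6% for the t-test, and 1 − 37/44 = 15.9% for the normal approximation.

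**The case against.** Four arguments can be made for the protocol.

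*The cause is not documented.* A reader might infer that the authors certainly multiplied by 1.2. The article does not establish this, because it shows no base number and no formula. Another route comes close: if the treated mean of 175.5 mL is rounded to 176 mL, the difference is 41 mL, n = 35.32 and 35.32 / 0.8 = 44.15, which is 44 to the nearest whole number. That route changes an input and rounds a required minimum down, so the ×1.2 explanation fits better, but it remains an inference. The shortfall does not depend on the cause, since both routes leave 44 too small for the stated 30% increase.

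*The gap is small and varies with convention.* This stands. By the normal approximation with an unrounded base, the gap is 2 women per group and 1.3 points of power. It reaches 4 women and 2.5 points only with the t-test and a base rounded up first. Taking the SD at 62 instead of 61.5 moves the unrounded base from 36.2 to 36.8, so uncertainty in a planning SD from one previous study could easily matter as much.

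*Losses for the primary outcome may be below 20%.* Weighing runs from 48 to 72 hours after delivery, and discharge is on the fourth day, so women are still on the ward. A reader might infer that the trial is underpowered. The documents do not support this: the shortfall arises only if more than about 14 to 16% lack primary data, and nothing shows that they will. This argument also stands, but it concerns what may happen. The sentence itself claims that 44 is sufficient at 20%, and no separate rate is given for the primary outcome.

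*The analysis is by intention to treat.* This does not close the gap. The sample-size paragraph itself budgets for withdrawals, and the article describes no method that would recover the missing volumes.

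**Conclusion.** Wrong as written, and minor. The claim that 44 per group is the minimum for 80% power after 20% withdrawal does not follow from the stated inputs; about 46 to 48 per group would be needed. If the whole 20% are lost, power is about 78 to 79% (77.5% t-test, 78.7% normal).

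This rests on reading 61.5 mL as an SD common to both groups, on equal losses in the two groups, and on withdrawn women contributing no primary outcome. It does not call the design, the recruitment target or the validity of the comparison into question.

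**What to change.** Keep 88 women and correct the sentence in the sample-size paragraph, for example: *Evaluable groups of 37 to 38 women give 80% power for a 40.5 mL difference (SD 61.5 mL, two-sided alpha 0.05). Randomising 44 per group allows for about 14% withdrawal; with 20% withdrawal (about 35 per group) power is about 78%.* Print the number before the allowance and the formula used, so that the figure can be reproduced.

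If the sponsor prefers to keep both 20% withdrawal and 80% power for the planned t-test, the number to state is 47 to 48 per group (94 to 96 in total), which means 6 to 8 more women.

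The recommended change is to the text only. It needs no added recruitment and leaves the analysis as it is. Its cost is a slightly less favourable stated power or withdrawal allowance.

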### Statistical analysis

IBM SPSS version 22 (SPSS: An IBM Company, New York, USA) will be used for statistical analysis. Two-tailed test is used in this study. Kolmogorov-Smirnov tests will be used to assess data distribution prior to statistical analysis. Chi-square test and Fisher’s exact test will be used for categorical variables such as percentage of satisfaction and side effects. Independent t-test will be used for parametric continuous variables such as the volume of the breastmilk. Mann-Whitney U test will be used for nonparametric variables when appropriate. A p-value <0.05 will be considered statistically significant. Analysis of the trial will be conducted by using intent-to-treat (ITT) analysis (Fig 2).

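### Maternal satisfaction is recorded on five ordered levels but assigned to chi-square/Fisher, which does not use the full ordering and costs power on this secondary outcome

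*Protocol article*

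**What the plan says.** The Protocol article's Materials and methods lists the secondary outcomes, among them "time to noticeable breast fullness, the maternal satisfaction, quality of life, side effects". Satisfaction is collected by telephone on postpartum day 7, and the response scale is given in full: "Satisfaction answer choices will consist of the following: very satisfied, satisfied, neutral, unsatisfied, and very unsatisfied". These five answers run in a clear order from best to worst.

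The Statistical analysis section then assigns the test by name: chi-square and Fisher's exact tests "will be used for categorical variables such as percentage of satisfaction and side effects". A rank test appears in the same section, but only in general terms: "Mann-Whitney U test will be used for nonparametric variables when appropriate". It is not tied to satisfaction. All tests are two-sided ("Two-tailed test is used in this study") and the threshold is common to all outcomes: "A p-value <0.05 will be considered statistically significant".

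The article gives no expected satisfaction distribution, no effect size or power for satisfaction, and no cut-point that would turn the five answers into one percentage. The 44 women per arm come from milk volume alone.

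**The concern.** The question behind this outcome is directional: are women given the active capsule more satisfied than women given placebo? The answers are ordered, so the natural signal is a shift along the scale. A chi-square or Fisher's exact test on the 2×5 table gives the same result if the five labels are shuffled. It spreads its power over patterns that do not answer the question, and its p-value alone does not say which arm did better. A dichotomised percentage does show direction, but it discards every difference within the merged levels.

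At stake is the chance of detecting a real, consistent shift in a patient-reported outcome when only about 35 to 44 women per arm contribute. Because satisfaction is named in the sentence on chi-square and Fisher's test, this is a stated choice of method and not a detail left to a fuller document.

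**Working it through.** **Numbers per arm.** The plan's own figure reproduces for the primary outcome. A 30% increase on 135.0 mL is 40.5 mL, so n = 2 × (1.960 + 0.842)² × 61.5² / 40.5² = 36.2 per arm, and 36.2 × 1.2 = 43.4, i.e. 44. With 20% withdrawal, 44 × 0.8 = 35.2, so about 35 to 44 women per arm would have a satisfaction answer. There is no planned figure for satisfaction to reproduce.

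**Model (assumed).** If C is the cumulative control probability of a given answer or better, the treated probability is OR × C / (1 − C + OR × C). For example, with C = 0.40 and OR = 2.5 the result is 1.0 / (0.6 + 1.0) = 0.625. The control distributions below, from very satisfied to very unsatisfied, are assumptions, as are the odds ratios. Tests are two-sided at 0.05, with 50,000 simulated trials per setting for the first four distributions. Several smaller separate runs were made for the fifth.

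**Reading 1: all five levels tabulated.** Power, 2×5 chi-square against tie-corrected Mann-Whitney, at OR 3:

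| Assumed control distribution | 35 per arm | 44 per arm |
|---|---|---|
| 20/20/20/20/20% | 49% vs 72% | 60% vs 81% |
| 10/20/40/20/10% | 46% vs 71% | 58% vs 80% |
| 25/45/20/7/3% | 44% vs 68% | 55% vs 78% |
| 40/45/12/2/1% | 45% vs 65% | 55% vs 74% |

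For 20/40/25/10/5% at 35 per arm, separate runs gave 31–32% vs 54–55% at OR 2.5, and 42–46% vs 67–70% at OR 3.

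Over 35 to 44 per arm and OR 2 to 3.5, the smallest gap in the first four distributions is 32.1 − 18.2 = 13.9 points (40/45/12/2/1%, OR 2, 35 per arm). The largest is 70.7 − 45.9 = 24.8 points (10/20/40/20/10%, OR 3, 35 per arm).

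**A check that needs no satisfaction distribution.** A 1-df test with 80% power has noncentrality (1.960 + 0.842)² = 7.85. A 4-df chi-square with the same noncentrality has 60% power. To regain 80% it needs 11.94, and 11.94 / 7.85 = 1.52, or about 52% more women. This treats the ordered test as capturing the whole signal.

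**Reading 2: a dichotomised percentage.** Power at 35 per arm, OR 2.5:

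| Assumed control distribution | Mann-Whitney | Cut: satisfied or better | Cut: very satisfied |
|---|---|---|---|
| 20/40/25/10/5% | 54–55% | 40–42% | 40–42% |
| 20/20/20/20/20% | 56% | 45% | 40% |
| 10/20/40/20/10% | 55% | 45% | 27% |
| 25/45/20/7/3% | 53% | 33% | 44% |
| 40/45/12/2/1% | 50% | 22% | 45% |

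The loss is about 13 points in the first row. In the last row it is 49.7 − 44.7 = 5 or 49.7 − 21.7 = 28 points, depending on the cut. Over all settings run for the last four distributions, it is about 7 to 44 points for the cut at satisfied or better, and about 3 to 33 points for the cut at very satisfied.

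**Type I error.** With no effect (OR 1), rejection was 3.3 to 5.0% for the 2×5 chi-square, 4.8 to 5.2% for Mann-Whitney and 4.6 to 6.0% for the dichotomies. None departs materially from 5%.

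**The case against.** The strongest reply is that the article speaks of a percentage of satisfaction, alongside side effects, which suggests one binary summary per arm. On that reading there is a single degree of freedom, the cut follows the order, direction is visible, and the thin lower categories are merged. This stands. A reader might infer that the plan commits to a 4-df test that cannot show direction, but the text does not establish that; it holds only if all five levels are tabulated. What does not follow is that the binary reading removes the problem. It still loses power against a rank test, and by how much depends on a cut-point that the article does not give.

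A reader might also infer that sparse cells make the analysis unsound. With an assumed 5% in the lowest category, 35 × 0.05 = 1.75 women are expected there per arm. But Fisher's exact test is named beside chi-square and deals with that.

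Three further points stand. The power figures rest on assumed distributions and a shift in one direction, which favours a rank test. At a small shift (OR 1.5, 35 per arm, 20/40/25/10/5% base) both tests are weak, about 8% against 15%. And satisfaction is one of several secondary outcomes with no power claim. The general mention of Mann-Whitney puts the remedy within the plan, but does not assign it to this outcome.

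**Conclusion.** The point holds as one of efficiency. The plan pairs an ordered five-level outcome with tests that do not use the full ordering, and an order-respecting test does better under either reading of the text. With five levels tabulated, the loss is about 14 to 25 power points over the range examined. With a dichotomy it runs from a few points to more than the 2×5 test loses, depending on the distribution and the cut. These sizes are conditional on assumed distributions and a proportional-odds shift, because the article supplies neither.

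It would go too far to call the planned tests invalid or the trial's conclusion threatened. Type I error is held near 5%, Fisher's test covers sparse tables, and neither the primary outcome nor the sample size depends on this choice. The change is worth making because it is nearly free.

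**What to change.** In the Statistical analysis section, remove satisfaction from the examples for chi-square and Fisher's test. State that the five-level score is compared between arms with the Mann-Whitney test, or with a proportional-odds model giving a common odds ratio with 95% confidence interval. Report the five percentages by arm descriptively, so that readers still see simple proportions. Keep chi-square/Fisher for side effects and for breastfeeding at 6 months.

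The cost is about one sentence, with no new data, visits or software. There are two small downsides: a rank or common-odds-ratio result is slightly harder to read than a single percentage, and the gain in power is realised only if satisfaction shifts in one direction.
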